### Maintenance Self-Efficacy: Stage 1/2

This question will be presented to subjects with the title 'Keeping up the good work'

How certain are you that you could overcome difficulties when trying to eat more healthily?

|                                                                                               |                 |                  |                  |                   |
|-----------------------------------------------------------------------------------------------|-----------------|------------------|------------------|-------------------|
| I am certain that I could overcome difficulties when trying to eat more healthily even if.... |                 |                  |                  |                   |
|                                                                                               | Not at all
1 | Barely true
2 | Mostly true
3 | Exactly true
4 |
| I don't see success at once                                                                   |                 |                  |                  |                   |
| I won't get support for my first attempts                                                     |                 |                  |                  |                   |
| It takes a long time to make it a habit                                                       |                 |                  |                  |                   |

### Recovery Self-Efficacy: Stage 1/ 2

This question will be presented to subjects with the title 'How do you feel about lapses?'

In spite of good intentions, lapses or relapses may occur. If your eating have become unhealthy, how confident are you that you can return to a healthier diet?

|                                                                             |                 |                  |                  |                   |
|-----------------------------------------------------------------------------|-----------------|------------------|------------------|-------------------|
| I'm certain I could start eating a healthier diet again even after I had... |                 |                  |                  |                   |
|                                                                             | Not at all
1 | Barely true
2 | Mostly true
3 | Exactly true
4 |
| occasional lapses during the week                                           |                 |                  |                  |                   |
| a full-blown relapse                                                        |                 |                  |                  |                   |

### ACTION PLANNING: Stage 2

These two questions will be presented to subjects with the title 'Planning'

|                                            |            |             |             |              |
|--------------------------------------------|------------|-------------|-------------|--------------|
| I now have my own plan regarding           |            |             |             |              |
|                                            | Not at all | Barely true | Mostly true | Exactly true |
| When to eat a healthier diet               |            |             |             |              |
| How to overcome my unhealthy eating habits |            |             |             |              |

### COPING PLANNING: Stage 1/2

|  |
|--|
|  |
|--|

| Have you thought about possible barriers that could interfere with eating a healthier diet? |            |             |             |              |
|---------------------------------------------------------------------------------------------|------------|-------------|-------------|--------------|
|                                                                                             | Not at all | Barely true | Mostly true | Exactly true |
| I have a detailed plan...                                                                   |            |             |             |              |
| How to avoid high-risk situations where the urge to eat unhealthy food is high              |            |             |             |              |
| How to arrange my daily routine to minimise the temptation to eat unhealthy food            |            |             |             |              |

## FEEDBACK QUESTIONS Stage 2

These two questions will be presented to subjects with the title 'Your Feedback'

| I found the information provided by the study so far: |                   |   |   |                |   |   |   |
|-------------------------------------------------------|-------------------|---|---|----------------|---|---|---|
|                                                       | Strongly Disagree |   |   | Strongly Agree |   |   |   |
|                                                       | 1                 | 2 | 3 | 4              | 5 | 6 | 7 |
| Trustworthy                                           |                   |   |   |                |   |   |   |
| Of personal relevance to me                           |                   |   |   |                |   |   |   |
| Enjoyable                                             |                   |   |   |                |   |   |   |
| Interesting                                           |                   |   |   |                |   |   |   |
| Contained a lot of new information                    |                   |   |   |                |   |   |   |
| Credible                                              |                   |   |   |                |   |   |   |
| Worrying                                              |                   |   |   |                |   |   |   |
| A wake up call                                        |                   |   |   |                |   |   |   |

## Intentions: Stage 1/2

This question will be presented to subjects with the title 'Dietary Beliefs'

Please rate your intentions to change the following aspects of your diet over the next two weeks.

Over the next four weeks I intend to....

|                                              | Strongly
1 | Strongly
2 | Disagree
3 | 4 | 5 | Agree
6 | 7 |
|----------------------------------------------|---------------|---------------|---------------|---|---|------------|---|
| Replace high fat with lower fat alternatives |               |               |               |   |   |            |   |
| Eat smaller portions of high fat foods       |               |               |               |   |   |            |   |
| Reduce the amount of bad fats in my diet     |               |               |               |   |   |            |   |

## General Health Behaviours: Stage 2

This question will be presented to subjects with the title 'Your General Health Behaviours'

Compared to usual, over the last four weeks did you.....

|                                   | A lot
less
1 | About the
Same
2 | A lot
more
3 | 4 | 5 | 6 | 7 |
|-----------------------------------|--------------------|------------------------|--------------------|---|---|---|---|
| Drink alcohol                     |                    |                        |                    |   |   |   |   |
| Use Cholesterol lowering products |                    |                        |                    |   |   |   |   |
| Find you weigh                    |                    |                        |                    |   |   |   |   |

|                           |  |  |  |  |  |  |  |
|---------------------------|--|--|--|--|--|--|--|
| Smoke                     |  |  |  |  |  |  |  |
| Take up physical activity |  |  |  |  |  |  |  |
| Eat a well-balanced diet  |  |  |  |  |  |  |  |
| Choose lower fat foods    |  |  |  |  |  |  |  |

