### **2.2 Secondary Objectives**

The secondary objectives of this study are to evaluate:

1. The effects of planning and SMS reminders on intentions, maintenance and recovery self-efficacy, action and coping planning and feedback of the intervention items.
2. The mediation effects of various constructs of the health action process approach (HAPA) Model (e.g. planning) on behaviour.

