### b) Intervention

In the main study phase, subjects will be randomly allocated into one of three different conditions: a) Control Group, b) Planning and c) Planning and SMS Reminders. Subjects in the experimental conditions will be first provided with information on a healthy diet, the importance of good fats in a person's diet and the link between cholesterol, diet and overweight.

Subjects in the planning condition will then identify a list of situations where they would like to change their dietary intake. They will then be asked to match these situations with a list of behaviours. They would be requested to choose pairs of situations and behaviours that they want

to change rather than ones that they are already doing (Appendix 4). The list of behaviours is based on the process of change model of Prochaska (1979). It includes strategies such as counterconditioning, stimulus control and use of helping relationships. A number of more nutritionally based behaviours have also been created with the help of an expert nutritionist and information from accredited sources such as the Food Standard's Agency 'eat well, be well' site (<http://www.eatwell.gov.uk/>). Once, they have made their selections they will be given the option to go back to improve their plan or revise their situation-solutions.

Subjects in the SMS reminders and planning condition will also follow the same process to choose their situation-solution pairs and then be provided with SMS reminders of these pairs over the course of the 4 weeks. Two SMS reminders will be sent per week. Subjects will be able to choose the time of the day they would like to receive the SMS reminder. Subjects will be also informed that use of their mobile number for the SMS reminders will be made only during the duration of the study and they will not be contacted any further upon completion of the study.

All subjects will be invited to answer a number of questions on their perceptions of the information received, intentions to make lifestyle changes, feelings of self-efficacy. Subjects in the control group will be told that they will be put on a waiting list and will receive further information in four weeks time.

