#### **7.1.2 Secondary**

The secondary endpoints are:

- a) Other health behaviours
- b) Intention to reduce saturated fat intake
- c) Maintenance and recovery self-efficacy
- d) Action and coping planning

e) Reaction to the intervention

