### **11.2 Data Analysis and Plan of Efficacy**

A full statistical analysis plan will be formulated in collaboration with [name] from the Unilever Statistics Group, Colworth Park. The effect of the design factors will be determined by comparing the proportion of subjects who have reduced their self-perceived saturated fat intake. Analysis of variance with baseline covariates will be conducted to analyse the behavioural (TIS, FFQ, portion sizes changes, other health behaviours) and social-cognitive measures (intentions, self-efficacy, planning, feedback). Baseline self-reported saturated fat intake will be included as a covariate for the analysis of the primary outcome measures. The stratification variables will be included in the models as will other covariates found significant at the 0.05 level. Comparisons between treatments will all be reported using two-sided significance levels (i.e. making no prior assumption about which treatment group will be most effective). Separate analysis of the effects of modifiers and mediators will be conducted in order to gain a better insight as to who benefits from the intervention.

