## PLAN

This is a summary of your plan to follow over the next two weeks:

| Situations                     | Solutions                                                 |
|--------------------------------|-----------------------------------------------------------|
| If I'm craving a high fat food | Then I will find out about a lower fat option             |
| If I'm having breakfast        | Then I will tell myself if I try hard I can eat healthily |
| If I had a hard day            | Then I will go for fruit                                  |

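### The intentions form, the only measure of a named secondary endpoint, gives a two-week horizon in its instruction and a four-week horizon in its item stem, so the score carries avoidable noise

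*Protocol*

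**What the plan says.** In the Protocol, Appendix 3, the form headed "Intentions: Stage 1/2" opens with the instruction "Please rate your intentions to change the following aspects of your diet over the next two weeks". The line directly below, which the three rated items complete, reads "Over the next four weeks I intend to". The items cover swapping to lower-fat alternatives, smaller portions of high-fat foods, and less bad fat in the diet, each on a seven-point agreement scale. The heading places the form at both time points.

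Appendix 3 contains no other intentions instrument. The score therefore carries secondary endpoint 7.1.2(b), "Intention to reduce saturated fat intake". It also serves the first objective in section 2.2, "The effects of planning and SMS reminders on intentions, maintenance and recovery self-efficacy, action and coping planning and feedback of the intervention items". Section 11.2 assigns the social-cognitive measures, intentions among them, to an analysis of variance that adjusts for baseline covariates.

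**The concern.** An intention score means something only in relation to a period. Here two adjacent lines, both read by the subject, name different periods for the same answers. One subject may rate a fortnight and another a month, and the same subject may read the form one way at Stage 1 and the other way at Stage 2. The form collects only the rating, so the period each subject had in mind cannot be recovered.

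At stake are the clarity of one secondary endpoint, some loss of precision in comparing arms on it, and a weaker link between the baseline score and the follow-up score if the Stage 1 value is used for adjustment. The protocol can remove the fault before launch. A statistical analysis plan cannot repair it afterwards.

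**Working it through.** The protocol states no figure for the intentions score, so there is nothing to reproduce. Its sample size statement (11.3) concerns self-perceived saturated fat only. The check is mainly textual.

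**1. Are there really two horizons on one form?** Yes. The instruction says two weeks and the stem says four. Both are participant-facing text, and neither is a record of superseded wording.

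**2. Which horizon fits the rest of the measurement plan?**

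| Place in the protocol | Period |
|---|---|
| Appendix 3, Intentions: item stem | four weeks |
| Appendix 3, Portion Changes | four weeks |
| Appendix 3, Perceptions of saturated fat intake | four weeks |
| Appendix 3, General Health Behaviours | four weeks |
| Protocol Summary and 1.3: timing of Time 2 | four weeks |
| Appendix 5: invitation and welcome page | four weeks |
| Appendix 3, Intentions: instruction | two weeks |
| 1.3: period for plans and SMS reminders | two weeks |
| 2.1: period in the primary aim | two weeks |
| 11.1: time of final assessment | two weeks |
| Appendix 4, Slide 3: plan summary | two weeks |
| 5.1 b): SMS reminders and control waiting period | four weeks |

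The companion questionnaires with a stated window all use four weeks. The intentions instruction is the exception among them. It also belongs to a wider conflict between two and four weeks that runs through the protocol.

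**3. Would settling the wider conflict correct the form?** Not by itself. Deciding when Time 2 falls or how long the reminders run leaves this printed line as it is, unless someone edits it.

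**4. How large could the noise be?** The protocol gives no input, so this is an assumption. Suppose a share *p* of subjects reads two weeks, the reading is unrelated to arm and to the true score, and the horizon shifts an answer by δ SD. The added variance, as a fraction of the variance under a single reading, is *p*(1 − *p*)δ². It is largest at *p* = 0.5, where it equals δ²/4.

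- δ = 0.1: 0.01/4 = 0.0025, so the standard error rises by √1.0025 − 1 = 0.1%.
- δ = 0.3: 0.09/4 = 0.0225, so the standard error rises by √1.0225 − 1 = 1.1%.

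These are effects before baseline adjustment. Relative to the smaller adjusted residual variance they would be somewhat larger, and shifts that vary between subjects would add more.

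**The case against.** Three points can be made against the concern.

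*The stem governs.* The four-week phrase is part of every rated sentence, while the two-week phrase is only a lead-in and looks like leftover wording. Many subjects may answer for four weeks without noticing. This limits the likely damage, but it does not make the form consistent.

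*It is one more instance of the wider timing conflict.* This is largely fair, and the line should be reconciled with the others. It still needs its own edit (step 3 of the working).

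*It is minor.* The form serves one of five secondary endpoints and neither primary endpoint, and its wording is the same in every arm. That is correct and sets the ceiling on the point.

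A reader might go further and infer bias between arms. Planning subjects are shown "This is a summary of your plan to follow over the next two weeks", while controls are told that they "will receive further information in four weeks time". On assumed inputs this can be made to look serious. A shift of 0.1 to 0.3 SD and a difference of 25 to 50 percentage points in the share reading two weeks give a spurious contrast of 0.1 × 0.25 = 0.025 to 0.3 × 0.50 = 0.15 SD. With about 500/3 ≈ 167 completers per arm, the unadjusted standard error is √(2/167) = 0.109 SD, and the 5% false-positive rate would become 5.6% to 27.8%. The arithmetic is right, but the documents do not support the mechanism:

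- The Protocol Summary and the Study Schematic place the Time 1 questionnaires before allocation, and 5.1 a) describes the social-cognitive questionnaire ahead of the intervention. On that order no arm-specific cue exists at Stage 1. Section 5.1 b) and Appendix 1 point the other way, so the order is unsettled.
- Section 5.1 b) mentions the controls' waiting-list message after the intentions questions, not before them.
- All arms share the four-week invitation and welcome page, and the SMS arm is described with both periods (1.3 and 5.1 b).
- At Stage 2, on the four-week timing, the plan slide is weeks old.

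Neither assumed input comes from the protocol, so the range should carry no weight.

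**Conclusion.** The contradiction is certain, and it sits in the only instrument for secondary endpoint 7.1.2(b) at both time points. Because the period a subject used is not recorded, the resulting measurement error cannot be undone after collection. What can be claimed is avoidable noise in the score and its baseline value. On the assumptions shown (even split, shift of 0.1 to 0.3 SD, reading unrelated to arm), the unadjusted standard error rises by about 0.1% to 1.1%. The larger cost is an endpoint whose time frame is not clearly defined.

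A difference in reading between arms is possible but not shown, and its size cannot be derived from the protocol. The point is worth correcting because the remedy is nearly free and available only before launch. It does not threaten the primary analysis.

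**What to change.** In the instruction of the intentions form, replace two by four, so that it agrees with its own stem, with the four-week windows of the other Appendix 3 forms, and with Time 2 as given in the Protocol Summary and section 1.3. Use identical wording at Stage 1 and Stage 2.

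Make this edit in the same pass that reconciles the protocol's other two-week and four-week statements: sections 1.3, 2.1, 5.1 b) and 11.1, and Appendix 4, Slide 3. It would help to state in that pass whether the Stage 1 intentions form comes before or after allocation, since the protocol gives both orders.

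The cost is one word in an online form before launch, plus approval of the amended text if ethical approval has already been given (Part III, 2.2). It needs no extra subjects, data or analysis.

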## APPENDIX 4- Planning

### Slide 1

# STEP 3: Make a Plan for a Healthier Diet

**PLANNING** is a great way to help you eat a more healthy diet.

The success of Planning lies in its simplicity.

## FOLLOW THESE STEPS TO MAKE A PLAN

In the next page you will be asked to:

- 1. Choose a situation** when you find it difficult to eat healthy (e.g. If I'm having lunch)
- 2. Choose a solution to your situation** (e.g. Then I will go for chicken instead of other fattier meats)
- 3. Repeat this three times** so that you choose 3 situations and 3 solutions that apply to you

**Don't go for things that you are already doing**

[figure not shown]

### Slide 2

In this page you will set your **THREE PLANS**. Please follow instructions in the bubbles. It might take a few seconds for the system to load each selection. There are no right or wrong choices!

| Situations                             |  | Solutions                                               |
|----------------------------------------|--|---------------------------------------------------------|
| If I go shopping                       |  | Then I will choose a lower fat spread                   |
| If I go for a dish with cheese         |  | Then I will choose a low fat dairy product              |
| If I'm getting a snack                 |  | Then I will go for chicken                              |
| If I'm having lunch/dinner             |  | Then I will find out about a lower fat option           |
| If I'm having breakfast                |  | Then I will go for oily fish                            |
| If I'm in a restaurant                 |  | Then I will go for fruit instead of chocolate/crisps    |
| If I'm having a good time with friends |  | Then I will not buy high fat foods to keep in the house |
| If I'm feeling down or upset           |  | Then I will tell myself I can eat healthy!              |
| If I'm craving a high fat food         |  | Then I will find something to distract myself           |
| If I'm feeling hungry                  |  | Then I will choose a lower fat cheese with it           |
| If I had a hard day                    |  | Then I will go for a smaller portion of the same food   |

|                                               |  |                                                 |
|-----------------------------------------------|--|-------------------------------------------------|
| If others around me are eating high-fat foods |  | Then I will go for a vegetable dish or soup     |
| If I want to have a lamb or pork dish         |  | Then I will distract myself with something else |

### Slide 3

## PLAN

This is a summary of your plan to follow over the next two weeks:

| Situations                     | Solutions                                                 |
|--------------------------------|-----------------------------------------------------------|
| If I'm craving a high fat food | Then I will find out about a lower fat option             |
| If I'm having breakfast        | Then I will tell myself if I try hard I can eat healthily |
| If I had a hard day            | Then I will go for fruit                                  |

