## 1.3 Brief Description of Intervention

To the best of our knowledge there are no studies that have tested online the combined effects of planning with SMS reminders in a more complex behaviour such as dietary changes. In the present study, the aim was to test for differences on the effects of three different conditions on saturated fat intake and the purchase of products that contribute to lowering or helping maintain a healthy diet.

At **Time 1**, subjects will be invited to participate in the study by an online recruitment agency, which will also carry out the screening process. Once, subjects have been accepted in the study they will be randomly allocated into one of three conditions. In the most advanced condition, subjects will be asked to form implementation intentions and be reminded of their plans by SMS reminders over the course of the two weeks. In the second condition, they will be asked to form plans on how to eat healthier over the course of two weeks. All conditions will be asked to fill out questionnaires on: a) a self-reported dietary intake questionnaire (Margetts et al, 1989) and b) a self-reported questionnaire on various social cognitive variables (e.g. intentions, self-efficacy). The Control Group (CG) will be only asked to fill out these questionnaires at this stage. All three groups will receive educational information on the importance of a healthy diet low in saturated fat and the association between high cholesterol and being overweight. A coupon of a cholesterol lowering product, with 50p off the face value, will be posted to all participants as a reward for successfully completing baseline assessments.

At **Time 2 (4 weeks later)**, subjects will be invited to fill out again the same dietary measures of food intake and an extension of the psychological determinants' questionnaire. Study subjects will be rewarded for their participation in the study (£15). This will be upon completion of study phase 2.

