#### Portion Changes: Stage2

This question will be presented to subjects with the title 'Portion Changes'

During the last 4 weeks, my portions of the foods below were:

| A lot smaller             | A lot bigger |   |   |   |   |   |   |
|---------------------------|--------------|---|---|---|---|---|---|
|                           | 1            | 2 | 3 | 4 | 5 | 6 | 7 |
| Meat dishes               |              |   |   |   |   |   |   |
| Cheese ordinary           |              |   |   |   |   |   |   |
| Cheese/egg meals          |              |   |   |   |   |   |   |
| Butter                    |              |   |   |   |   |   |   |
| Whole Milk                |              |   |   |   |   |   |   |
| Bacon                     |              |   |   |   |   |   |   |
| Beef- roast/steak         |              |   |   |   |   |   |   |
| Pork-roast/chops          |              |   |   |   |   |   |   |
| Lamb-roast/chops          |              |   |   |   |   |   |   |
| Chocolate                 |              |   |   |   |   |   |   |
| Crisps and savoury snacks |              |   |   |   |   |   |   |

### Perceptions of saturated fat intake: Stage 1/ 2

These two questions will be presented to subjects with the title 'Eating Habits'

|                                                            |                   |                |   |   |   |   |   |  |
|------------------------------------------------------------|-------------------|----------------|---|---|---|---|---|--|
|                                                            | Strongly Disagree | Strongly Agree |   |   |   |   |   |  |
| I have eaten foods high in bad fats in the last four weeks | 1                 | 2              | 3 | 4 | 5 | 6 | 7 |  |

|                                                                      |       |            |   |   |   |   |   |  |
|----------------------------------------------------------------------|-------|------------|---|---|---|---|---|--|
|                                                                      | Never | Frequently |   |   |   |   |   |  |
| How often did you eat foods high in bad fats in the last four weeks? | 1     | 2          | 3 | 4 | 5 | 6 | 7 |  |

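### The protocol gives the SMS reminders two different durations, and its two-week plan does not match the four-week period the outcome items ask about

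*Protocol*

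**What the plan says.** **Plan period.** Appendix 4, Slide 3 heads the participant's plan with "This is a summary of your plan to follow over the next two weeks". Section 1.3 agrees for the planning-only condition: "they will be asked to form plans on how to eat healthier over the course of two weeks".

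**Who sees the plan screen.** Section 5.1, b) Intervention, states: "Subjects in the SMS reminders and planning condition will also follow the same process to choose their situation-solution pairs". No separate screen is given for the SMS arm, so by inference both planning arms see the two-week wording.

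**Reminder period.** Section 1.3 says SMS-arm subjects will "be reminded of their plans by SMS reminders over the course of the two weeks". Section 5.1 says they will "then be provided with SMS reminders of these pairs over the course of the 4 weeks", at a rate of two messages a week.

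**Outcome window.** The Stage 2 portion-size form in Appendix 3 begins "During the last 4 weeks, my portions of the foods below were". Both items of the saturated fat perception measure also refer to the last four weeks.

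**Intention horizon.** The lead-in to the intention item in Appendix 3 reads "Please rate your intentions to change the following aspects of your diet over the next two weeks". The stem directly below it refers to the next four weeks.

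**The concern.** The length of the intervention is part of its definition. Here the reminders have two lengths, the plan follows the shorter one, and the outcome forms follow the longer one. The SMS schedule cannot be programmed unambiguously from this text, and a participant's instructions cannot be corrected once they have been shown.

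Section 1.2 gives the purpose of the study as testing whether planning combined with SMS reminders has stronger effects than planning alone or no intervention. Two things are at stake:

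- the size of the planning effect, if the outcome period extends beyond the period the plan was set for;
- the meaning of the difference between the two planning arms, if reminders continue after the period printed on the plan.

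The intention item is a smaller case of the same fault. Respondents who answer for two weeks and respondents who answer for four cannot be told apart in the data.

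**Working it through.** The protocol offers no figure of its own to reproduce on this point. The check sets the stated periods side by side and counts messages. It takes the final assessment at four weeks, as in the Protocol Summary, section 1.3 and the Appendix 5 invitation.

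**Inputs**

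| Element | Place | Period |
|---|---|---|
| Plan, as shown to participants | Appendix 4, Slide 3 | 2 weeks |
| Plan, planning-only condition | Section 1.3 | 2 weeks |
| SMS reminders | Section 1.3 | 2 weeks |
| SMS reminders | Section 5.1 b) | 4 weeks |
| SMS rate | Section 5.1 b) | 2 per week |
| Portion-size and two-item saturated fat outcomes | Appendix 3 | last 4 weeks |
| Intention item, lead-in | Appendix 3 | next 2 weeks |
| Intention item, stem | Appendix 3 | next 4 weeks |

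**Message count** = rate × weeks

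- Section 1.3 reading: 2 × 2 = 4 messages. After the two-week plan period: 2 × (2 − 2) = 0.
- Section 5.1 reading: 2 × 4 = 8 messages. After the two-week plan period: 2 × (4 − 2) = 4, which is 4/8 = half.

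The two readings differ two-fold in exposure (8/4 = 2).

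**Match to the outcome window**

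- Section 1.3 reading: plan and reminders both cover 2 of the 4 weeks asked about. The remaining 4 − 2 = 2 weeks, half the window, lie after the stated intervention period. This is the same in both planning arms, so it creates no imbalance between them. It can dilute either arm's effect against control if use of the plan declines after week 2.
- Section 5.1 reading: the reminders cover all 4 weeks, while the plan text in both planning arms covers 2. In weeks 3 and 4 the SMS arm is still prompted about a plan whose printed period has passed, and the planning-only arm receives no prompt.

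The protocol gives no information on how far people keep to a plan after its stated period, so neither the dilution nor the extra effect of late reminders can be quantified from it.

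**The case against.** The strongest reply concerns the comparison between the two planning arms. A reader might infer that the contrast is confounded because the SMS arm has a longer plan. The documents do not support that. Both arms follow the same planning process and, by inference, see the same screen, so the reminders are the difference between them. If reminders keep a plan in use after week 2, that is itself an effect of reminding. Section 1.1 presents reminders as a way to enhance the impact of implementation intentions, and prolonged use is one way they could do so. The asymmetry also arises only on the section 5.1 reading; on the section 1.3 reading both arms have the same two-week period. This part of the reply stands, and the randomised comparison of the packages is valid.

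A reader might also infer that planning-only subjects are told to stop at week 2. No text says so. The screen sets a period and gives no instruction to end. The Appendix 5 invitation and screening introduction describe the study as lasting four weeks, and so does the intention stem. A sharp lapse at two weeks would be an assumption.

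It can further be said that this is one document-wide slip. Section 2.1 (primary objective) and section 11.1 (follow-up) also say two weeks, against four in the Protocol Summary, section 1.3 and Appendix 7. The slips may share a cause, but correcting the follow-up time in section 11.1 would leave the plan screen, the reminder period in section 1.3 and the intention lead-in unchanged.

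The reply does not remove the contradiction between sections 1.3 and 5.1, the mismatch between a two-week plan and four-week outcome items, or the double horizon in the intention item.

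**Conclusion.** The point holds as a contradiction about the length of the intervention, not as a claim of bias in the randomised comparison. What the documents establish is a two-fold uncertainty in SMS exposure (4 or 8 messages), a stated plan period covering half of the outcome window, and an intention item with two horizons.

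The consequence depends on the reading:

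- With two weeks of reminders, both planning arms are assessed over a window twice their stated period, and the effect against control can be diluted.
- With four weeks of reminders, the packages can be compared validly, but an SMS benefit may partly reflect use of the plan beyond its stated period. What the benefit says about reminding within that period is then less clear.

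This rests on three assumptions: both planning arms see Slide 3 as printed, messages are sent at the stated weekly rate throughout, and the final assessment is at four weeks. No effect size can be attached. The fault is worth correcting before launch because analysis cannot repair it afterwards.

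**What to change.** Before launch, reconcile section 1.3, section 5.1 b), Appendix 4 Slide 3 and the intention item in Appendix 3. The plan period, the reminder period and the intention horizon should each be stated once, in the same terms wherever they recur, and be consistent with the period the outcome items ask about. Which duration applies is for the sponsor to decide. If the sponsor wants the periods to differ, the protocol should say so and say how the difference between the two planning arms is then to be read.

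The cost is a few words on one web screen, one questionnaire line and two protocol sentences, submitted as a short amendment. If the outcome items have to change to match, their wording goes into the same amendment. The sample size does not change.
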